
### Implementation outcomes

Acceptability of the intervention to women and healthcare professionals.Feasibility of implementing the intervention.

### Sample size

We used data from a recent meta-analysis,^19^ which reported that 39% of women were anaemic at 6 weeks postpartum, as the control event rate. A sample size of 697 participants per group would provide 90% power to detect a relative reduction of 20% for intravenous iron to reduce the event rate of anaemia at 6 weeks postpartum to 30%, after accounting for 10% loss to follow-up. Power calculations assume a 1:1 randomisation ratio to each of the two treatment arms. 1400 women will be enrolled into the trial.

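### The sample-size statement attaches two different effects to one power claim: 39% to 30% is a 23% relative reduction, not 20%, and the 90% power holds only for the former

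*Protocol article*

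**What the plan says.** All the design figures are in the Sample size section of the protocol article. The control rate comes from a meta-analysis reporting that "39% of women were anaemic at 6 weeks postpartum, as the control event rate". The section then states that "A sample size of 697 participants per group would provide 90% power". The effect to which that power refers is described as "a relative reduction of 20% for intravenous iron to reduce the event rate of anaemia at 6 weeks postpartum to 30" per cent. The number per group already allows for 10% of women being lost. Allocation is 1:1, and the total is rounded up: "1400 women will be enrolled into the trial".

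The Sample size section gives no alpha. The Statistical methods and analysis section gives a two-tailed 0.05, adjusted to 0.0492 at the final analysis because of one O'Brien-Fleming interim look. The same section says that the primary endpoint will be reported as a relative risk with a 95% CI.

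**The concern.** One sentence expresses the target both as a relative reduction and as an event rate on intravenous iron. Given the 39% control rate, the two do not agree. Rounding does not close the gap: 31.2% rounds to 31%, and 23.1% rounds to 23%.

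The difference matters because required sample size rises steeply as the effect shrinks, so one N cannot give 90% power for both. The relative figure is also the one readers are likely to carry forward, since the primary result will be a relative risk. Read on that scale, the sentence says that the trial was powered at 90% for RR 0.80, when the calculation supports about RR 0.77. At stake is whether the stated operating characteristic of the sole primary outcome is true.

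**Working it through.** **Inputs**
- Control rate p1 = 0.39; rate on intravenous iron p2 = 0.30, or a 20% relative reduction; 697 per group; 90% power; 10% loss; 1:1 allocation; 1400 in total (Sample size).
- Two-sided alpha 0.05 (Statistical methods and analysis). Applying this alpha to the sample-size calculation is an assumption; 0.0492 is tried as a variant.
- Evaluable per arm: 697 × 0.9 = 627. From 1400 enrolled: 700 × 0.9 = 630.

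**Step 1. Are the two effects the same?**
- 20% relative reduction: 0.39 × 0.80 = 0.312.
- 39% to 30%: 1 − 0.30/0.39 = 0.231, so RR = 0.77.

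They are not.

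**Step 2. Which effect reproduces the stated N?** Two-proportion normal approximation with pooled variance under the null, where p̄ is the mean of p1 and p2:

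n per arm = [1.960·√(2p̄(1−p̄)) + 1.282·√(p1(1−p1) + p2(1−p2))]² / (p1−p2)², then divided by 0.9 for loss.

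- 39% versus 30%: p̄ = 0.345, so n = (1.960 × 0.6723 + 1.282 × 0.6693)² / 0.09² = 584.2. That is 585 evaluable, or 650 enrolled.
- 39% versus 31.2%: p̄ = 0.351, so n = (1.960 × 0.6750 + 1.282 × 0.6727)² / 0.078² = 784.8. That is 785 evaluable, or 873 enrolled.

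| Enrolled per arm for 90% power | 39% vs 30% | 39% vs 31.2% |
|---|---|---|
| Alpha 0.05 | 650 | 873 |
| Alpha 0.05, continuity correction | 675 | 902 |
| Alpha 0.0492 | 653 | 877 |
| Alpha 0.0492, continuity correction | 677 | 905 |

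Neither column contains 697 exactly. The first column falls 3% to 7% short of it (677/697 = 0.97; 650/697 = 0.93). The second exceeds it by 25% to 30% (873/697 = 1.25; 905/697 = 1.30). A target of 30.3%, which rounds to 30%, gives 627 evaluable and 697 enrolled without continuity correction. That is a 22.3% relative reduction (1 − 0.303/0.39). The 30.3% is an inference and is not stated in the article.

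**Step 3. Power at the stated N.** Power = Φ{[(p1−p2)·√n − 1.960·√(2p̄(1−p̄))] / √(p1(1−p1) + p2(1−p2))}, with n = 627:

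- 39% versus 30%: (0.09 × 25.04 − 1.960 × 0.6723) / 0.6693 = 1.399, so power is 91.9%.
- 39% versus 31.2%: (0.078 × 25.04 − 1.960 × 0.6750) / 0.6727 = 0.937, so power is 82.6%.

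| Power | 39% vs 30% | 39% vs 31.2% |
|---|---|---|
| 627 per arm, alpha 0.05 | 91.9% | 82.6% |
| 630 per arm, alpha 0.05 | 92.0% | 82.7% |
| 627 per arm, alpha 0.0492 | 91.8% | 82.4% |
| 627 per arm, continuity correction | about 91% | about 81% |

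On the log relative risk scale, power for 31.2% with 627 per arm is about 82%. Ignoring loss altogether (697 evaluable) gives 86.3% for 31.2%, still below 90%.

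**The case against.** The strongest reply is that the sentence names the 30% event rate as explicitly as the 20% reduction. A two-proportion calculation works from the two event rates, and for 39% versus 30% the 90% claim is met with a little to spare. The stated 697 also points to about 30% as the value used, since a trial sized for 31.2% would have needed some 870 to 905 per arm. On this view the design is sound and only a descriptive label is wrong. That reply stands, and it limits the point to the label.

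It does not remove the point. As printed, the sentence claims 90% power for a 20% relative reduction, and the design does not have that power.

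A reader might infer two stronger things that the article does not support:
- **That the trial is underpowered, at 83% rather than 90%.** This follows only if a 20% reduction was the intended target. Nothing in the article shows that it was, and the stated N suggests otherwise.
- **That a null result would be misread as excluding a 20% reduction.** This is speculative. The Statistical methods and analysis section commits to a relative risk with a 95% CI, and that interval, not the planned power, shows which effects are excluded.

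**Conclusion.** The statement is wrong as written, in a limited way. With 627 evaluable women per arm, the 90% claim is met for 39% versus 30% (about 91-92%) and not met for a 20% relative reduction (about 81-83%). If the true effect were a 20% reduction, the trial would miss it about 17 times in 100, not 10. The most likely explanation is a wrong or loosely rounded label on a calculation made for about 30%. That is an inference from the N, and only the sponsor can confirm it.

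The conclusion rests on two-sided alpha 0.05, on loss handled by dividing by 0.9, and on a standard two-proportion test. Neither a continuity correction nor alpha 0.0492 changes it. Severity is minor to moderate: one design figure is misstated, while enrolment, the primary outcome, the analysis and the stopping boundary are unaffected.

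**What to change.** Keep 1400 women and have the sponsor confirm which effect was powered.

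- If it was 30%, restate the detectable effect, for example: 697 per arm (627 evaluable after 10% loss) gives at least 90% power, two-sided alpha 0.05, to detect a reduction from 39% to 30%, a relative reduction of about 23% (RR 0.77).
- If a 20% relative reduction was the intended target, give the event rate as 31.2% and the power as about 83%.

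Quoting power for both effects is optional. Whichever figure is confirmed should appear in the same form in the SAP and the results paper. The Trial status section projected that recruitment would end by June 2024, before the article appeared in August 2024, so those two documents are the practical places for the correction.

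The cost is one sentence. Under the first option the stated detectable effect becomes slightly less favourable; under the second, the stated power does. Nothing changes in enrolment, conduct or analysis.

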### Recruitment

Randomisation and enrolment will occur between 6 and 48 hours after birth. Postpartum women within this timeframe (6–48 hours postpartum) are being screened for eligibility, provided with information about the trial, and given time to consider their participation. They are randomised to one of the two treatment groups after obtaining written informed consent.

### Randomization and allocation

Individual randomisation and allocation concealment are done using ‘Sealed envelope’ a web-based randomisation software; https://www.sealedenvelope.com/access/ in a 1:1 ratio in blocks stratified by study site.

### Blinding

It will be difficult to blind the treatment allocation as the intervention is administered intravenously, while the control is administered orally. However, the primary outcome is an objective measure determined by laboratory evaluation. For the secondary outcomes that are subjective: the EPDS, Quality of Life questionnaire, fatigue scale, Maternal Infant Bonding questionnaire and adverse event report form, the research nurses performing data collection for these outcomes will be blinded to group allocation. Data on treatment compliance will be collected only after all other outcome data for the woman’s visit has been completed and submitted.

Only the senior data manager has unblinded and full access to the database. The trial statistician has access to blinded data to support the Data Safety and Monitoring Board (DSMB) and Trial Steering Committee (TSC). All other investigators only have access to blinded summary reports.

### Participants’ timeline

Women will be enrolled between 6 and 48 hours after birth and followed up until 6 months postpartum (figure 3).

**Figure 3 F3:**
[figure not shown]
Participant flow diagram.

### Retention strategies

To minimise loss to follow-up, counselling sessions are extended to partners and family members when necessary during follow-up visits. Reminders for follow-up appointments are sent via short message service and telephone. The details of participants’ home addresses are also collected at enrolment and reviewed before each visit. For participants who cannot be reached, community tracking is done (home-based monitoring system designed to locate participants in their homes or place of work). Consent for community tracking is obtained at enrolment.

### Data collection methods

REDCap (Research Electronic Data Capture V.13.8.3), developed by Vanderbilt University in Nashville, Tennessee, USA, is a secure web-based application used to capture data for clinical research, create databases and manage projects. It is being used to collect all relevant study data. Electronic case report forms, surveys and other data collection instruments were developed and refined in the study database to collect information at enrolment, follow-up, end of study visits and for adverse events. Other study instruments in the trial database are the EPDS, fatigue scale, MIB scale and quality of life scale e-forms. Designated investigators and study staff will enter the information in real time as required by the protocol into the electronic forms on the REDCap and source documents as indicated.

### Data management

Data are collected using electronic case report forms at various participant study visits using assigned participant IDs and uploaded in real-time to the REDCap database after being checked by the study site coordinator. Data management is guided by standard operating procedures that will be periodically revised and communicated with the study staff.

### Statistical methods and analysis

Primary analyses will be conducted with the intention to treat principle. Categorical variables will be expressed as frequencies and percentages. Continuous variables will be presented as means (SD) or medians (interquartile ranges) depending on whether they are normally distributed or not. The effect of intravenous iron (vs oral iron) on the primary endpoint will be analysed using log-binomial regression models to obtain relative risks, 95% CIs and p values. The impact of clustering by site will be evaluated by comparing to logistic generalised linear mixed models using likelihood ratio tests, and the more parsimonious model presented. The extent to which inclusion of baseline covariates modifies the precision of estimates will be explored. Generalised linear mixed models will be used to estimate the effect of the treatment arm on repeated measures of haemoglobin and iron status biomarkers. The proportion of participants who are anaemic or iron deficient, and the proportion of participants who achieve anaemia correction at 6 weeks and 6 months follow-up will be compared. Subgroup analyses will be conducted to compare study findings by region (Lagos, Kwara, Kano and Rivers), mode of birth (caesarean vs vaginal birth) and by the occurrence of primary postpartum haemorrhage. A two-tailed test of hypothesis will be performed based on an alpha level of 0.05. R and RStudio (2020)http://www.rstudio.com/ will be used for statistical analysis.^20^ An interim analysis will be conducted by an independent statistician after achieving 50% of the sample size and data presented to the Data Safety and Monitoring Board (DSMB). Based on O’Brien-Fleming method,^21^ the threshold for significance of the primary endpoint at the interim analysis will be alpha=0.0054. The clinical trial will be terminated if the null hypothesis is rejected. The alpha level for the analysis at the end of the study will be adjusted to 0.0492 based on alpha adjustment based on O’Brien-Fleming method.

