### Clinical outcomes

The primary outcome is the proportion of participants who are anaemic (haemoglobin < 110 g/L) at 6 weeks postpartum.

Secondary outcomes:

Change in mean serum ferritin, serum transferrin, serum iron and % transferrin saturation at 2 weeks and 6 weeks postpartum.Proportion of women with postpartum depression, measured using the Edinburgh Postnatal Depression Scale (EPDS)^15^ at 6 weeks and 6 months postpartum.Change in mean postpartum haemoglobin levels at 2 weeks and 6 weeks postpartum.Achievement of a non-anaemic state (Hb ≥110 g/L) at 6 months postpartum.Prevalence of moderate/severe anaemia at 6 weeks and 6 months postpartum. Moderate anaemia is defined as haemoglobin level 70–<100 g/L and severe anaemia as haemoglobin level <70 g/L.Need for blood transfusion after iron treatment during the first 6 weeks postpartum.Prevalence of fatigue at 6 weeks and 6 months postpartum, measured using the Fatigue Severity Scale (revised FSS-5R version).^16^Proportion of women with secondary postpartum haemorrhage after treatment. This will be defined as excessive bleeding requiring surgical intervention or blood transfusion from 24 hours after delivery until 12 weeks postpartum.Proportion of infants being breastfed (exclusive and any) at 6 weeks and 6 months postpartum.Prevalence of impaired maternal-infant bonding at 6 weeks and 6 months postpartum measured using the Mother-to-Infant Bonding Scale.^17^Incidence of confirmed or suspected maternal infection within 6 weeks of birth, as defined by a new prescription of antibiotics for presumed perineal wound-related infection, endometritis or uterine infection, urinary tract infection or other systemic infection (clinical sepsis).Incidence of hypophosphataemia at 2 weeks and 6 weeks postpartum. We will measure vitamin D, alkaline phosphatase, procollagen type I N-terminal propeptide (P1NP), fibroblast growth factor 23 (FGF23), calcium, phosphate, all of which are biomarkers of phosphorus homeostasis and bone turnover. Hypophosphataemia is defined as serum phosphate level <2.5 mg/dL (0.81 mmol/L). Mild hypophosphataemia as 2–2.5 mg/dL (0.65–0.81 mmol/L), moderate as 1–2 mg/dL (0.32–0.65 mmol/L) and severe as <1 mg/dL (0.32 mmol/L).Incidence of early neonatal death, defined as death of newborn from enrolment of the mother to before seven completed days.Incidence of late neonatal death, defined as death of the newborn after seven completed days of birth to before 28 completed days.Incidence of infant death, defined as death from enrolment before the age of 6 months.Incidence of postnatal maternal death from enrolment up to 6 weeks and at 6 months postpartum.Incidence of adverse drug events.Quality of life measured using the WHO Quality of Life BREF^18^ at 6 weeks and 6 months postpartum.

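### A likelihood ratio test for site clustering can decide whether the primary result is reported as a relative risk or an odds ratio, and whether site is modelled at all

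*Protocol article*

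**What the plan says.** All references are to the protocol article.

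- **Clinical outcomes** defines a binary primary endpoint: "The primary outcome is the proportion of participants who are anaemic (haemoglobin < 110 g/L) at 6 weeks postpartum".
- **Statistical methods and analysis** says that the treatment effect on this endpoint "will be analysed using log-binomial regression models to obtain relative risks, 95% CIs and p values". No site term is stated for this model.
- The next sentence of that section brings in a second model: "The impact of clustering by site will be evaluated by comparing to logistic generalised linear mixed models using likelihood ratio tests". Of the two candidates, just one is to be reported, since that sentence closes with the words "and the more parsimonious model presented".
- Covariates are treated separately and only as exploration: "The extent to which inclusion of baseline covariates modifies the precision of estimates will be explored".
- **Randomization and allocation** says that women are allocated "in a 1:1 ratio in blocks stratified by study site". **Study sites** gives 20 sites in four states, at three levels of care.
- **Sample size** expresses the target effect as a relative reduction, from 39% anaemic in the control group to 30%.

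Nothing in the article fixes the relative risk as the reported measure whichever model is chosen, or says that a logistic result would be converted back to a relative risk.

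**The concern.** The two candidate models differ in two ways at once. The log-binomial model has a log link, gives a relative risk and has no stated site term. The logistic mixed model has a logit link, gives an odds ratio conditional on site, and models site. One test on the trial data is used to choose between them, and one model is presented. A question about clustering can therefore settle a different question, namely which effect measure heads the paper.

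At stake are the definition of the primary treatment effect, which ought to be fixed before the data are seen, and the handling of the factor that stratified the randomisation. The endpoint is common, so the odds ratio lies well away from the relative risk and is easily misread as one. It is also not the quantity on which the trial was sized.

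**Working it through.** The article gives no figure for this point. The check uses its design rates and, where it is silent, stated assumptions.

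**1. What the test compares.** With arm as the only term, the log-binomial and the ordinary logistic model each have two parameters for two groups. Both fit the two observed proportions exactly, so their maximised likelihoods are equal. Setting the site variance in the logistic mixed model to zero gives that ordinary logistic model. The likelihood ratio statistic is therefore a test of zero site variance, on the boundary of the parameter space. Its reference distribution is a 50:50 mixture of zero and chi-square with 1 df (5% cut-off 2.706); using 3.84 is conservative. The test carries no information on which link or effect measure is preferable.

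**2. What changes if the model changes** (rates from Sample size).

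- RR = 0.30/0.39 = 0.77.
- OR = (0.30/0.70)/(0.39/0.61) = 0.4286/0.6393 = 0.67.
- Read as a risk ratio, the OR turns a 23% reduction into an apparent 33%.
- For an exact 20% relative reduction, the intervention rate is 0.8 × 39% = 31.2%, giving RR 0.80 and OR (0.312/0.688)/(0.39/0.61) = 0.71.
- Holding the overall rates at 39% and 30%, the site-conditional OR moves from 0.67 to 0.65 as the intraclass correlation (ICC) rises from 0 to 0.10.

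**3. How often the mixed model would be chosen, if the test decides.** The article gives neither between-site variation nor site sizes, so both are assumed. Evaluable women per arm: 697 × 0.90 = 627; over 20 equal sites, about 31 per arm per site. ICC = σ²/(σ² + π²/3), where σ is the site SD on the logit scale.

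| Site SD | ICC | Chosen at cut-off 3.84 (two sets of 300 trials) |
|---|---|---|
| 0 | 0 | 1%, 2% |
| 0.2 | 0.012 | 20%, 25% |
| 0.3 | 0.027 | 63%, 67% |
| 0.5 | 0.071 | 98%, 98% |

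With the boundary cut-off 2.706 (20 sites of 63 women, 150 trials per setting, with and without a treatment effect), the mixed model was chosen in 3% to 6% of trials at ICC 0, 59% at 0.02, 96% to 99% at 0.05 and 100% at 0.10.

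**4. What happens to the inference.**

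- Ignoring site overstates the standard error of the log relative risk by about 0.3% to 2.2% for site SD 0.2 to 0.5.
- On the logit scale the direction reverses: about 0.120 unadjusted against 0.122 to 0.125 with site as fixed effects.
- At two-sided 0.0492, the unadjusted RR and the site-adjusted logistic analysis disagreed on significance in 0.2% to 1.0% of 600 simulated trials per setting.
- At 39% against 30%, rejection rates for the unadjusted, mixed and selected analyses all lay between 0.89 and 0.94. Differences in type I error could not be resolved: with 150 trials the simulation error near 5% is √(0.05 × 0.95/150) = 1.8 percentage points.

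**5. The literal reading.** The log-binomial model has fewer parameters, so it is always the more parsimonious. If that alone decides, it is always presented, the test does nothing, and no stated primary model includes site.

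**The case against.** The strongest reply is that the article names one measure for the primary endpoint, the relative risk, and never says that an odds ratio will be reported. On the literal reading of parsimony no switch ever occurs. Even if the mixed model were chosen, a relative risk can be derived from it by standardisation, and such detail may sit in an analysis plan not shown here. The inference barely moves either way.

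Much of this stands, and it rules out several stronger readings that a reader might infer:

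- *That the plan certainly switches to an odds ratio.* The sentence is ambiguous; the switch follows only if the test result decides.
- *That the likelihood ratio test is invalid because the models are not nested.* This applies only once covariates enter, and the article merely explores those. With arm alone the test is a usable boundary test.
- *That site is dropped from the model.* The log-binomial model never has a stated site term to drop.
- *That intervals or error rates are seriously wrong.* The figures above show small effects, and the loss of precision on the relative-risk scale is conservative.

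What does not stand is the suggestion that nothing needs changing. The article does not merely omit detail; it states a selection rule. Under one reading the data can choose the effect measure. Under the other the stated test is idle and the stratification factor is left out. An analysis plan that always reports a standardised relative risk would remove the first problem, but would have to add to or override this sentence; the handling of site would still need fixing.

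**Conclusion.** The point holds as a should-fix. The rule leaves the primary effect measure open to a data-dependent choice and makes the handling of the randomisation stratum either conditional on a test or absent.

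The size of the switch is RR 0.77 against OR 0.67 at the design rates, which follows from the article's own numbers. Its frequency is illustrative only: it rests on assumed between-site variation, equal site sizes and the reading under which the test decides. Facilities in four states and at three levels of care make some variation plausible, but the article does not quantify it. The effect on standard errors and on significance is small, and no inflation of type I error has been shown. The case therefore rests on prespecification and clear reporting rather than on a wrong conclusion about efficacy, and for that reason it is not a must-fix.

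**What to change.** Replace the selection sentence before any unblinded comparative analysis:

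- State the relative risk as the primary effect measure, in line with the sample size basis.
- Estimate it from a log-binomial model that includes site, whatever any test of clustering shows.
- Name the fallback in advance, for example modified Poisson regression with robust standard errors and the same terms, to be used only if the log-binomial model does not converge.
- Report the logistic mixed model as a sensitivity analysis, never in place of the relative risk.

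The cost is about one sentence and no extra data. The downside is that a log-binomial model with 20 site levels may well fail to converge, so the fallback may be needed. That too would be settled on the data, but by a stated convergence rule, and the reported measure remains the relative risk.

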### Eligibility criteria

Inclusion criteria:

Women aged between 15 and 49 years and between 6 and 48 hours after birth.Moderate or severe anaemia (haemoglobin <100 g/L), confirmed by Hemocue haemoglobinometer.Able and willing to give written informed consent.

Exclusion criteria:

Blood transfusion, for any indication, within the last 3 months.Symptomatic anaemia and a need for urgent correction.Known haemoglobinopathy such as sickle cell disease, haemoglobin C disease.Clinically confirmed malabsorption syndrome.Known hypersensitivity or contraindication to any form of iron treatment, study drug or any of its excipients.Self-reported pre-existing maternal depression or other psychiatric illness as evidenced by a YES response to any history of psychiatry ward hospitalisation, psychiatry medications, behavioural changes or past consultation with psychiatric services.Severe allergic conditions such as severe asthma, eczema, or other atopic conditionKnown autoimmune conditions for example, systemic lupus erythematosus, rheumatoid arthritis or known severe drug allergies.Planning to move or reside outside the research area within the study period.

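### The primary model commits to no baseline covariate and leaves the status of the adjusted estimate open, although baseline haemoglobin and site are available for every woman

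*Protocol article*

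**What the plan says.** The protocol article, under Statistical methods and analysis, assigns the primary endpoint (anaemia at 6 weeks) to log-binomial regression by intention to treat, reported as a relative risk. No baseline covariate is named for that model. Two further sentences bear on it:

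- Clustering by site is to be judged by likelihood ratio tests against logistic mixed models, and the simpler model is the one reported.
- On covariates, the whole provision is "The extent to which inclusion of baseline covariates modifies the precision of estimates will be explored".

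Neither sentence lists covariates, mentions baseline haemoglobin, or says whether an adjusted or an unadjusted relative risk is the primary result.

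Elsewhere, Eligibility criteria require "Moderate or severe anaemia (haemoglobin <100 g/L), confirmed by Hemocue haemoglobinometer", so every randomised woman has a baseline value of the variable that defines the outcome. Randomization and allocation states that blocks are stratified by study site. The Sample size section works from two event rates and assumes no gain from covariates.

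**The concern.** Baseline haemoglobin is the obvious candidate predictor of haemoglobin below 110 g/L six weeks later, and it is recorded before randomisation. A primary model that includes it gives a relative risk at least as precise, in a trial of this size, as one that does not. Site stratifies the randomisation, and an analysis would normally reflect that. Here, covariates are left to an exploration and site to a test on the observed data.

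Two things are at stake. One is efficiency: information the trial already holds is not committed to the primary estimate. The other is clarity: if the adjusted and unadjusted results differ, the article does not say which one answers the primary question.

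**Working it through.** **Inputs from the article.** Control rate: "39% of women were anaemic at 6 weeks postpartum, as the control event rate". Intervention rate and loss: "to reduce the event rate of anaemia at 6 weeks postpartum to 30%, after accounting for 10% loss to follow-up". 697 per group, 90% power, 1:1 allocation, 1400 enrolled. Test: "A two-tailed test of hypothesis will be performed based on an alpha level of 0.05"; for the final look, "The alpha level for the analysis at the end of the study will be adjusted to 0.0492".

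**Assumed input.** The correlation ρ between baseline and 6-week haemoglobin among enrolled women is not given. The range used is 0.2 to 0.5, with 0.6 as an outer case.

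**Step 1: the plan's own figure.** With p₁ = 0.39, p₂ = 0.30, mean p̄ = 0.345 and difference d = 0.09, power is Φ(z), where

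z = [d√n − 1.96·√(2p̄(1−p̄))] / √(p₁(1−p₁) + p₂(1−p₂)).

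After 10% loss, n = 697 × 0.9 = 627. Then z = (0.09 × 25.04 − 1.96 × 0.6723) / 0.6693 = (2.254 − 1.318) / 0.6693 = 1.40, so power is 91.9% (91.8% at alpha 0.0492). The unadjusted test meets the stated 90%. The figure of 697 is not reproduced exactly: the same formula needs 650 per group after loss, and 677 with continuity correction at alpha 0.0492. The difference is on the safe side.

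With 1400 enrolled, n = 700 × 0.9 = 630 and power is 92.0%. For a literal 20% relative reduction, p₂ = 0.39 × 0.8 = 0.312, and n = 630 gives z = (0.078 × 25.10 − 1.96 × 0.6750) / 0.6727 = 0.94, or 82.7%.

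**Step 2: variance removed by baseline haemoglobin.** This was simulated with 630 women per arm and 1,500 runs per setting. The 6-week value was a normal variable with correlation ρ to baseline, cut to give the planned event rates. The unadjusted log relative risk was compared with a log relative risk standardised over baseline haemoglobin from a logistic model. Variance reduction = 1 − (SE adjusted / SE unadjusted)². For 39% against 30% and ρ = 0.5, that is 1 − (0.0725/0.0787)² = 0.15. At ρ = 0 the reduction was below 0.1%.

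**Step 3: power after adjustment.** Effective n = 630 / (1 − reduction), put back into the formula of Step 1.

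| ρ (assumed) | Variance reduction | Effective n per arm | Power, 39% vs 30% | Power, 39% vs 31.2% |
|---|---|---|---|---|
| none | 0 | 630 | 92.0% | 82.7% |
| 0.2 | 2.5% | 646 | 92.6% | 83.7% |
| 0.3 | 5.5% | 667 | 93.4% | 84.8% |
| 0.5 | 15.3% | 744 | 95.5% | 88.4% |
| 0.6 | 22.4% | 812 | 96.9% | 90.9% |

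Power was taken from the variance ratio because rejection rates from 1,500 runs carry a standard error of about one percentage point (√(0.83 × 0.17 / 1500) ≈ 0.010), as large as the gain at low ρ. The table covers haemoglobin only. No gain is claimed for site, because the article gives nothing on how much event rates vary between sites.

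**The case against.** The strongest reply is that this is a journal article, and that a covariate list is properly left to the full protocol or the analysis plan. That stands for the list: its absence is no error. It does not cover what the article does state, which is an exploratory role for covariates and a test-based rule for site. An analysis plan faithful to those two sentences would still leave both open.

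The reply is also right on three stronger readings that a reader might infer:

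- *That adjustment is post hoc.* It is not; the exploration is announced in advance.
- *That covariates will be chosen by the precision or p value they give.* The covariate sentence contains no selection rule and does not say that an adjusted result may replace the unadjusted one. It can be read as a supportive analysis. The text leaves the status open; it does not prescribe a data-driven choice.
- *That the trial is underpowered without adjustment.* At the stated rates it is not. The 82.7% figure comes from reading the 20% relative reduction literally, whereas 39% to 30% is a reduction of 0.09/0.39 = 23%. That mismatch in the Sample size section is a separate matter.

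Finally, the gain may sit at the low end. Entry is cut at 100 g/L, which narrows the spread of baseline values and may weaken the correlation. At ρ of 0.2 to 0.3 the gain is only about one to two percentage points of power.

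**Conclusion.** The point holds as a missed efficiency together with an unfixed status for the adjusted estimate. It is not a bias or an invalid test. The unadjusted randomised comparison is sound and has about 92% power at 39% against 30%.

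Under an assumed correlation of 0.2 to 0.5, adjusting for baseline haemoglobin adds about 0.6 to 3.5 percentage points of power at the stated rates, and about 1 to 6 points at 31.2%. These sizes rest on the assumed correlation, on a normal model for haemoglobin and on 10% loss; the article supplies only the last. They were computed for a standardised relative risk. Other adjusted relative-risk estimators were not simulated.

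The direction does not depend on those assumptions: a pre-specified prognostic covariate costs essentially nothing when it turns out weak and helps when it is not.

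**What to change.** In Statistical methods and analysis, replace both the covariate sentence and the preceding sentence on site clustering. Changing only the covariate sentence would leave two conflicting rules for site. Suggested text:

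> The primary relative risk is adjusted for baseline haemoglobin (continuous) and site, whatever the observed precision or site variation; the unadjusted relative risk is a sensitivity analysis. If the log-binomial model does not converge, modified Poisson regression with robust standard errors (or a relative risk standardised from a logistic model) will be used.

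The fallback matters because a log-binomial model with a continuous covariate and 20 sites may well fail to converge.

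The cost is two sentences and a matching entry in the analysis plan. No new data are needed, since haemoglobin and site are known for every woman at randomisation. The change should be dated before any outcome comparison by arm is seen by those who make it, and the same model should be used at the interim and final analyses.
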